### Recruitment and consent

Participants will be recruited from approximately 40 research centres within the United Kingdom under the guidance of the NCRI CLL sub-group. The recruitment target requires that 188 participants be recruited into the trial, 94 in each arm.

Patients will be approached during standard clinic visits for management of CLL and provided with verbal and written details about the trial. Informed consent will be collected by principal investigators and co-investigators at the participating hospitals before any trial-specific investigations. Participants are able to withdraw from treatment and follow-up at any stage of the trial. Participants will also be approached for the UK CLL Trials Biobank, as discussed in the “Sub-studies” section below.

### Randomisation

Following confirmation of eligibility and informed consent, MRD-positive participants will be randomised into the trial by an authorised staff member at the trial research site. Randomisation will be performed centrally using the Leeds Clinical Trials Research Unit (CTRU) automated 24-hour telephone registration and randomisation system. Participants will be randomised on a 1:1 basis to receive either obinutuzumab consolidation or no treatment. Participants will be informed of their treatment allocation in this open study.

A computer-generated minimisation program that incorporates a random element will be used to ensure treatment groups are well-balanced for the following participant characteristics: bone marrow MRD level at entry (≤0.3%, >0.3%), number of lines of previous therapy (one, more than one), age group (≤65, >65 years), sex (male, female), Binet stage of disease prior to most recent CLL therapy (A progressive or B, C) and previous rituximab (yes, no).

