## Background

Chronic lymphocytic leukaemia (CLL) is the most common adult leukaemia. The CLL8 trial [1, 2] has shown that even though almost double the number of patients receiving fludarabine, cyclophosphamide and rituximab (FCR) achieved minimal residual disease (MRD) negativity (defined as <0.01% CLL cells) compared with those receiving fludarabine and cyclophosphamide, once low-level MRD was achieved, both arms showed the same prognostic significance. This indirectly implies that the depth of the remission may be more important than the type of treatment given to attain that remission. Attainment of MRD negativity has also been demonstrated as an independent predictor of overall survival (OS) and progression-free survival (PFS) even with a variety of different treatment approaches and regardless of the line of therapy [3].

The researchers in the U.K. National Cancer Research Institute (NCRI) CLL207 phase II trial [4] assessed whether participants with low levels of disease could attain MRD negativity following consolidation therapy with alemtuzumab. The results showed good efficacy, with 39 (83%) of 47 participants who were consolidated attaining MRD negativity. Overall, 38% remained MRD-negative in the peripheral blood 6 months after therapy, which may be the true MRD-negative population because this represents the time for redistribution of the disease among various compartments following antibody treatment. After a median follow-up of 44 months, the participants who were MRD-negative 6 months after treatment had a significantly increased PFS time compared with those participants who were MRD-positive, with a median PFS at 3 years of 94.4% in MRD-negative participants compared with 60.0% in MRD-positive participants (*p* = 0.004). However, alemtuzumab had a significant toxicity profile, with 22 serious adverse event (SAEs), 4 of which were clinically unacceptable (1 pneumocystis pneumonia, 1 parainfluenza-related death and 2 Epstein-Barr virus-related transformed diseases), reported in 17 (36.2%) participants.

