### Trial population

Patients who are eligible for the trial must be at least 18 years old, have previous confirmation of CLL, have undergone between one and three regimens of chemotherapy previously ending between 3 and 24 months before enrolment, have a peripheral B-cell count of <5 × 10^9^/L, have a response to the most recent chemotherapy treatment for CLL with PR, complete remission with incomplete marrow recovery (CRi) or CR. The patient must also be capable of giving written consent and have a World Health Organisation (WHO) performance status of 0 or 1.

Patients with any of the following characteristics are excluded from the trial: disease progression after response to last therapy, active infection, previous anaphylaxis to monoclonal antibodies, previous treatment with obinutuzumab, central nervous system involvement in CLL, mantle cell lymphoma, other severe concurrent diseases or mental disorders that could interfere with their ability to participate in the study (including moderate or worse cardiac diseases), known HIV positivity, positive serology for hepatitis B or C virus, persisting severe pancytopenia (neutrophils <0.5 × 10^9^/L or platelets <50 × 10^9^/L) or transfusion-dependent anaemia, vaccination with a live virus within 28 days, active haemolysis (patients with haemolysis controlled with prednisolone at a dose 10 mg or less per day can be entered into the trial), creatinine and bilirubin less than two times the upper limit of normal, previously treated with an allogeneic stem cell transplant, pregnant or lactating women, or women/men who are capable of conceiving children and who are unwilling to use appropriate medically approved contraception during and for 18 months after receiving treatment.

Once participants provide consent for the trial, peripheral blood will be tested for MRD. Patients who are MRD-negative will not be eligible for randomisation but will still be followed annually for MRD. Patients who are MRD-positive will have bone marrow and trephine samples tested centrally to confirm MRD level in the aspirate, a stratification factor for randomisation. To be randomised, participants must have an MRD-positive peripheral blood sample between 3 and 24 months since completing the last treatment for CLL and be confirmed as MRD-positive in the bone marrow. Participants must also have clinically and radiologically confirmed absence of lymphadenopathy (largest lymph node 1.5 cm or less in minimum diameter).

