### Sample size

The overall sample size of the trial is powered for the phase III primary endpoint of PFS. An internal literature review investigating patients who have received up to three lines of previous therapy of any type and who responded to their most recent therapy with at least a PR suggested that 3 years is a reasonable estimate for median PFS in the control population (i.e., no consolidation), which translates to approximately 2 years from the time the participants are randomised (because it will be 3–24 months after previous therapy). An important clinical improvement would be an increase in median PFS from 2 to 3.3 years, a relatively large improvement, because consolidation is given at a time when patients would otherwise be in remission and treatment-free. The trial is powered to test the null hypothesis of no difference in PFS between the treatment arms, with a two-sided 5% level of significance and 80% power. Assuming 3 years of recruitment, 3 years of follow-up and allowing for a 5% drop-out rate, 188 participants are required (94 per arm) in order to observe 120 progression/death events. Losses to follow-up for the primary endpoint are expected to be extremely uncommon due to the short treatment duration and straightforward and regular follow-up schedule. A formal interim analysis on PFS will be carried out and reported to the data monitoring and ethics committee (DMEC) when half the required number of events have been observed (60 events).

The O’Brien and Fleming alpha-spending function [11] will be used to adjust for multiple testing to conserve the overall type I error, which recommends that the interim results be compared with a *p* value of 0.005, and the final analysis results are then compared with a *p* value of 0.047.

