### Primary endpoint analyses

The phase II primary endpoint of MRD negativity in each stage of the phase II part of the trial will be assessed once 9 and 23 participants have received at least 4 weeks of obinutuzumab treatment and been followed until 6 months post-randomisation. The phase III primary endpoint of PFS will be assessed once 120 events (progressions/deaths) have been observed overall. A formal interim analysis will be carried out when 60 events have been observed overall in order to allow large differences between the trial arms to be reported early (Fig. 4). PFS is defined as the time from randomisation to first documented evidence of progression or death. Participants not having progressed or died or who are lost to follow-up at the time of the phase III analyses will be censored at the last date they were known to be alive and progression-free. For the analysis of primacy, we will use a Cox proportional hazards model [15] to compare the trial arms, adjusting for the minimisation factors, to calculate the HR and corresponding 95% CIs. The *p* value to assess for statistical significance will be compared with 0.047 to account for the formal interim analysis. In addition, median survival estimates with corresponding 95% CIs, as well as Kaplan-Meier curves [16], will be produced by trial arm.

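### Optional, cheap gain: add continuous log10 marrow MRD at entry to the Cox models, which as written use only the 0.3% minimisation split

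*Protocol article*

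**What the plan says.** Under Randomisation, one of the six minimisation factors is "bone marrow MRD level at entry (≤0.3%, >0.3" (per cent), a two-level factor.

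Under Primary endpoint analyses, PFS is compared with a "Cox proportional hazards model [15] to compare the trial arms, adjusting for the minimisation factors". Secondary endpoint analyses uses the same adjustment for overall survival (OS) and treatment-free survival (TFS). Neither section names another MRD term for these comparisons of the randomised arms.

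Under Trial population, patients with MRD-positive blood have "bone marrow and trephine samples tested centrally to confirm MRD level in the aspirate, a stratification factor for randomisation". To be randomised they must also "be confirmed as MRD-positive in the bone marrow". A centrally measured marrow level should therefore exist for every randomised participant.

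The Background draws this inference from an earlier trial: "This indirectly implies that the depth of the remission may be more important than the type of treatment given".

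**The concern.** The trial is built on the idea that depth of remission matters, yet the efficacy models as written keep only one yes/no item about depth at entry. The two classes are wide. The Background defines MRD negativity as below 0.01%, so the lower class can span log10(0.3/0.01) = 1.5 logs. No numerical upper limit on marrow MRD is printed for entry, so everything above 0.3% forms one class.

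If hazard rises steadily with log MRD, variation within each class stays unmodelled. In a Cox model that pulls the estimated treatment hazard ratio (HR) somewhat towards 1 and lowers power. At stake is efficiency in the PFS comparison and, by the same mechanism, in OS and TFS. Efficiency is worth having here: the Discussion reports difficult recruitment, and Trial status shows closure after two years (February 2015 to February 2017) against three assumed under Sample size.

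**Working it through.** **Inputs from the protocol.** Median PFS: "an increase in median PFS from 2 to 3.3 years", so HR = 2/3.3 = 0.606. Two-sided 5%, 80% power, 120 events, 188 participants (94 per arm), 3 years' recruitment plus 3 years' follow-up, 5% drop-out, final p-value threshold 0.047.

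**Step 1: reproduce the design.** Schoenfeld events = 4(1.960 + 0.842)² / (ln HR)².

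- HR rounded to 0.60: 31.4/0.261 gives 121 events. With exponential PFS and uniform accrual the event probability is 0.691, so 121/0.691 gives 176, and 176/0.95 gives 186 participants. Power at 120 events is 79.9%.
- HR 0.606: 31.4/0.251 gives 126 events. With event probability 0.693, 126/0.693 gives 182, and 182/0.95 gives 192 participants. Power at 120 events is 78.3%.

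The stated 120 and 188 are reproduced closely, and the calculation contains no covariate.

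**Step 2: split against continuous MRD.** Simulated trials had 188 participants, analysis at the 120th event, p < 0.047, and arms balanced within the 0.3% split. *Assumed*, because the protocol does not say: log10 MRD normal with SD 0.8, median 0.3%, truncated to 0.01%–30%; treatment HR 0.606 conditional on MRD; hazard log-linear in MRD. There were 8,000 trials per row (4,000 in the first).

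| HR per 10-fold MRD | Split | Continuous instead of split | Difference (points) |
|---|---|---|---|
| 1.0 | 77.4% | 77.4% | 0.0 |
| 1.25 | 77.0% | 77.1% | 0.1 |
| 1.5 | 75.8% | 77.0% | 1.2 |
| 2.0 | 73.8% | 77.1% | 3.3 |
| 3.0 | 69.2% | 76.6% | 7.4 |

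Moving the assumed median MRD between 0.1% and 1% gives about 0 to 1 point up to a gradient of 1.5, 3 to 5 at 2, and 7 to 9 at 3. At gradient 2 the mean estimated HR is 0.615 with the split and 0.603 with continuous MRD.

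In events, at gradient 2: required information scales with (z for the 0.047 threshold + z for power)². That is (1.986 + 0.742)²/(1.986 + 0.637)² = 1.08, or about 8% of 120, roughly 10 events.

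**Step 3: validity.** With no treatment effect, both adjusted models reject in 4.6% to 5.0% of trials against the nominal 4.7%.

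**Step 4: a step at 0.3% instead of a gradient.** Replacing the split by continuous MRD then loses power: 77.4% falls to 75.8% for a step HR of 2, and 77.7% to 73.6% for a step HR of 3.

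**Step 5: keep the split and add log10 MRD.** This is a separate set of simulations.

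| True MRD effect | Split only | Split plus log10 MRD | Difference (points) |
|---|---|---|---|
| None | 75.9% | 75.7% | −0.2 |
| 1.5 per 10-fold | 76.4% | 77.5% | +1.1 |
| 2 per 10-fold | 74.1% | 77.6% | +3.5 |
| 3 per 10-fold | 67.8% | 75.8% | +8.0 |
| Step HR 2 at 0.3% | 76.0% | 75.7% | −0.3 |
| Step HR 3 at 0.3% | 76.3% | 75.6% | −0.7 |

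Absolute levels differ between the two sets by up to about 1.5 points, so only differences within a row should be read. Adding the term keeps nearly all of the gain under a gradient and limits the loss under a step to less than 1 point.

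**The case against.** **The coding is inferred.** The article does not state the functional form of the covariates and defers to a final analysis plan that is not shown. That plan could already use the continuous value. This stands as a caution. But the factor is defined with two levels, and the models are said to adjust for the factors, so the split is the natural reading of what is written.

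**The planned analysis is sound.** Adjusting for minimisation factors in the form used to allocate is conventional, and type I error is held. This stands in full. Chance imbalance within a class is ordinary random imbalance that the error rate already covers.

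**Planned power is not undermined.** A reader might infer from the first table that the split leaves the trial below its 80%. The documents do not support that. The sample size uses no covariates, and its medians are most naturally population medians, which imply a marginal HR. On that reading, at a gradient of 2, power is about 78% unadjusted, 83% with the split and 86% with continuous MRD. The planned model already improves on the design.

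**The gradient is unknown.** The Background's 94.4% against 60.0% at 3 years compares MRD-negative with MRD-positive patients after alemtuzumab. It says nothing about a gradient among MRD-positive patients before consolidation. The spread is also unknown. Entry requires a response without later progression, and the objectives describe low levels of MRD, so very high marrow values may be rare even without a printed limit. This stands, and it is why no single loss can be quoted.

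**Replacing the split could backfire.** A reader might conclude that the split should be dropped from the models. Step 4 shows that this can cost up to about 4 points if risk changes at 0.3%, and the protocol does not say which shape is true. The objection no longer applies if the continuous term is added and the split kept.

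**Conclusion.** As written, the PFS, OS and TFS models use only the 0.3% split of a marrow measurement available for every randomised participant. That is a valid choice which may forgo power for PFS: about 0 to 1 point for gradients up to 1.5-fold per 10-fold MRD, 3 to 5 points at 2-fold, and 7 to 9 points at 3-fold. These figures assume a log-linear effect and a log-normal MRD distribution with SD 0.8 and median between 0.1% and 1%; none of this is given in the protocol. OS and TFS share the mechanism but were not simulated. Neither a claim that the primary analysis is wrong nor a claim that the trial is underpowered for this reason would be justified. The point is a cheap, optional improvement.

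**What to change.** Keep the 0.3% factor in the minimisation and in the Cox models. Before any look at PFS, including the interim analysis at 60 events, pre-specify log10 marrow MRD at entry as an additional continuous covariate in the PFS, OS and TFS models. State how values at the assay limits are handled. Report the models with the minimisation factors alone as a sensitivity analysis.

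The cost is analysis wording and one extra parameter per model, with no new data collection. The loss is below 1 point of power if MRD is not prognostic or acts as a step at 0.3%.

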### Protecting against bias

This trial cannot be blinded, because the two treatment arms are substantially different. Treating consultants need to be aware of the drugs being administered to be able to treat reactions to treatment accordingly. The trial researchers will use an automated randomisation service incorporating randomisation by minimisation, and analyses will be done on an intention-to-treat (ITT) basis. The trial is administered by the chief and principal investigators and the CTRU in accordance with good clinical practice (GCP) guidelines. The assessment of response in the peripheral blood and the bone marrow for MRD will be centralised in a single laboratory, thereby providing standardisation for all assessments.

### Baseline assessments

Assessments to be performed prior to the participant starting treatment are a complete physical examination, WHO performance status, serology for hepatitis B and C virus, local haematology and biochemistry, a pregnancy test (for women of childbearing potential), an assessment of disease using blood, bone marrow aspirate, trephine, computed tomographic (CT) scan and QoL questionnaires. *See* the schedule of enrolment, interventions and assessments in Figs. 2 and 3. Some of these assessments will have already been carried out to confirm eligibility for randomisation. Where these assessments are done within 4 weeks of starting treatment, the eligibility assessments will be used for baseline. Where they fall outside this time frame, they will be repeated for baseline.

### Intervention

Participants randomised to obinutuzumab consolidation will receive 100 mg of intravenous (IV) obinutuzumab on day 1 and 900 mg on day 2. The remaining course of treatment will be 1000 mg IV on days 8, 15, 22 (weekly), 36, 50, 64 and 78 (2-weekly). Participants randomised to no consolidation therapy will receive no treatment.

Participants will be assessed for their suitability for treatment within 1 week before each obinutuzumab treatment. At minimum, tests will be performed to ensure that dose delays or reductions are implemented and that concomitant medications are administered as per protocol.

Prior to medication, analgesic/antipyretic (equivalent to 1000 mg of paracetamol) will be administered before each treatment. Antihistamine (equivalent to 10 mg of cetirizine) will be administered prior to days 1 and 2 of treatment and for remaining treatments for participants with an infusion-related reaction (IRR) (Common Terminology Criteria for Adverse Events [CTCAE] [13] grade 1 or higher) to the previous infusion. Corticosteroid infusion (equivalent to 100 mg of prednisolone) will be administered for days 1 and 2 and for participants with a grade 3 IRR with the previous infusion or participants with a lymphocyte count >25 × 10^9^/L before treatment. No concomitant cytotoxic agents, radiotherapy or vaccination with live viruses should be given.

### Management of toxicity

#### IRRs

For grade 4 IRRs, the infusion will be stopped and therapy discontinued. For grade 3 IRRs, the infusion will be temporarily interrupted and symptoms treated. Upon resolution of grade 3 symptoms, infusion will be restarted at no more than half the rate being used at the time that the IRR occurred, and, if the participant does not experience any IRR symptoms, infusion rate escalation may be resumed at the increments and intervals appropriate for the treatment dose. For grades 1–2 IRRs, the infusion rate will be reduced and symptoms treated. Upon resolution of symptoms, the infusion will be continued, and, if the participant does not experience any IRR symptoms, infusion rate escalation may resume at the increments and intervals appropriate for the treatment dose. Treatment may be discontinued due to poor tolerability/toxicity at the discretion of the treating physician. The guidance in the next sub-sections is applied to manage toxicity.

#### Haematological toxicity

Participants who experience grade 3 thrombocytopenia (platelets <50 × 10^9^/L) should be withdrawn from obinutuzumab because this toxicity is potentially a result of obinutuzumab. Participants who experience grade 3/4 neutropenia (neutrophils <1.0/<0.5 × 10^9^/L) should be closely monitored. The use of granulocyte colony-stimulating factor is recommended to maintain the neutrophil count above 1.0 × 10^9^/L. Treatment with obinutuzumab should be delayed until neutrophils are > 1.0 × 10^9^/L.

#### Non-haematological toxicity

If hypersensitivity to obinutuzumab occurs (typically occurring after previous exposure to obinutuzumab), the infusion should be stopped and treatment permanently discontinued. Participants with a known immunoglobulin E-mediated hypersensitivity to obinutuzumab should not be treated. Obinutuzumab should not be administered in the presence of a severe infection. Prophylactic therapy aimed at preventing a recurrence of a diagnosed infection should be instituted if clinically indicated. For treatment of tumour lysis syndrome, electrolyte abnormalities should be corrected, renal function and fluid balance monitored and supportive care administered, including dialysis as indicated.

#### Progressive multifocal leukoencephalopathy (PML)

Cases of progressive multifocal leukoencephalopathy (PML) have been reported in patients treated with anti-CD20 antibodies, including obinutuzumab. Treatment with obinutuzumab should be withheld during the investigation of potential PML and permanently discontinued in the event of a confirmed diagnosis.

#### Hypotension

Hypotension may occur during obinutuzumab infusions. Therefore, withholding of antihypertensive treatments should be considered for 12 hours before the obinutuzumab infusion, during the obinutuzumab infusion and for the first hour after administration. Patients with a history of cardiac disease should be monitored closely. A participant should permanently discontinue obinutuzumab treatment in the following situations:For grade 4 infusion-related symptoms, patient should be withdrawn immediately, and treatment must be discontinued permanentlyFor grade 3 infusion-related symptoms at re-challenge, patient must be withdrawn immediately, and treatment must be discontinued permanentlyGrade 3 or 4 cytopenia that has not resolved to grade 2 or lower and delays treatment of the next dose by 4 weeksGrade 2 or higher non-cytopenic toxicity that does not resolve to grade 1 or lower/baseline and delays treatment of the next dose by 4 weeks

